## Abstract

**Background:**

Informal carers (*i.e.,* family members or friends) of patients with heart failure are ill-prepared and under-supported for their caregiving role. To address this issue, the HEart faiLure carer support Programme was co-designed with carers and healthcare professionals, with pilot testing demonstrating intervention feasibility and acceptability. In the current article, we present the study protocol for evaluating the implementation and impact of the HEart faiLure carer support Programme in real-world, clinical settings across the United Kingdom (ClinicalTrials.gov ID: NCT07373041).

**Methods:**

A mixed-method, implementation study adopting a multi-centre, prospective cohort study design, with nested process and economic evaluations will be conducted. Nurses will deliver the HEart faiLure carer support Programme to 180 carers of patients with symptomatic heart failure across five sites spanning three nations of the United Kingdom (Northern Ireland, England, and Scotland). The patients (approximately 180) of carers enrolled in the project will be invited to provide outcome data. Recruited carers will receive weekly, nurse-led, online support group sessions and supplementary, self-directed educational resources (a booklet and website) for six weeks. Quantitative (*i.e.,* questionnaires and logs) and qualitative (*i.e.,* interviews) data will be collected from carers, patients, and healthcare professionals throughout the study. These data will evaluate the acceptability, fidelity, context, economic cost, and impact of HEart faiLure carer support Programme delivery in real-world clinical settings. An integrative analysis with mapping to the Consolidated Framework for Implementation Research and Normalisation Process Theory domains will be conducted, which will identify key synergies across quantitative and qualitative data sets.

**Discussion:**

The results will elucidate the factors underpinning successful intervention translation to clinical practice and identify any required contextual adaptations, along with generating preliminary evidence of intervention impact. These findings will inform a large-scale, type 2 hybrid study, advancing the HEart faiLure carer support Programme towards routine rollout across the United Kingdom.

## 1.0 Introduction

The global prevalence of heart failure (HF) is approximately 55.5 million, with this condition affecting more than one million individuals in the United Kingdom (UK) [1]. Effective self-management by these patients constitutes a key strategy for reducing hospital readmissions and improving quality of life (QoL) [2]. As HF progresses, self-management of symptom burden becomes increasingly challenging, often resulting in patients relying on support from informal carers (*i.e.,* family members or friends) [2]. However, previous research has comprehensively reported that these carers experience diminished mental and physical health and QoL, which correlates with the physical and emotional challenges of their caring role and the health status of the patient they care for [3,4].

The vital role fulfilled by carers in supporting patients with self-management is reflected in the European Society of Cardiology guidelines for HF treatment [2]. However, given the challenges faced, these carers require improved education and emotional support for sufficient empowerment in their caregiving role [3–7]. A recent systematic review and meta-analysis demonstrated a scarcity of interventions supporting carers of patients with HF, with the few studies available showing insignificant results and poor reporting of intervention development [8]. Moreover, there were no supportive interventions co-designed with carers in the UK to target their specific psychoeducational needs and requirements [8].

To address this significant area of unmet need, our research team systematically co-developed the ‘HEart faiLure carer support Programme (HELP)’ according to the UK Medical Research Council (MRC) framework for developing and evaluating complex interventions [9]. The intervention development process is comprehensively reported elsewhere [10]. In summary, previous evidence and theory [3,4,8] underpinned an interdisciplinary stakeholder group (carers, healthcare professionals, and academics) who co-developed and refined the design and content of HELP using an inclusive, sequential process [10]. This resulted in the production of a nurse-led, psychoeducational intervention comprising weekly online support group sessions and self-directed educational resources (booklet and website) delivered over a six-week period.

Following HELP development, a convergent, mixed-method, pilot study was conducted in the UK [10]. This research demonstrated that HELP is feasible and acceptable for carers of patients with HF, with participants highly rating the usefulness of the intervention. Moreover, there was preliminary evidence of potential improvements in carer preparedness and knowledge; emotional wellbeing; and empowerment in their care giving role [10]. However, there is uncertainty whether the findings of this pilot study can be replicated in the real-world environment, and the key factors underpinning successful integration of HELP into clinical environments are unclear. In this article, we report the study protocol for evaluating the implementation and impact of HELP in clinical practice, which will inform advancements of HELP towards routine rollout across the UK.

### 1.1 Aim

The overarching aim is evaluating the implementation and impact of HELP in real-world clinical settings across the UK.

### 1.2 Objectives

1)Evaluate the multi-faceted implementation strategy via a process evaluation of acceptability, fidelity, and context of HELP delivery across real-world clinical sites.2)Estimate the economic cost of HELP implementation.3)Explore the short and long-term impact of HELP on outcomes for carers and patients.

## 2.0 Methods

This study protocol is reported in accordance with the Standard Protocol Items: Recommendations for Interventional Trials (SPIRIT) guidelines (Fig 1 and S1 Checklist) [11] and the Standards for Reporting Implementation Studies (StaRI) (S2 Checklist) [12]. This study was registered on ClinicalTrials.gov (ID: NCT07373041). Queen’s University Belfast will lead all aspects of the study and serve as the sponsor.

**Fig 1 pone.0347037.g001:**
[figure not shown]
SPIRIT 2025 schedule of enrolment, interventions, and assessments. **Legend:** HELP = HEart faiLure carer support Programme; ZBI-12 = Zarit Caregiver Burden Interview Short Form; PCS = Preparedness for Caregiving Scale; QoL = Quality of Life; SF-12 = 12-Item Short Form Survey; HADS = Hospital Anxiety and Depression Scale; PSS-10 = Perceived Stress Scale; MSPSS = Multidimensional Scale of Perceived Social Support; MLHFQ = Minnesota Living with Heart Failure Questionnaire; EQ-5D-5L = EuroQol Five Dimension Questionnaire; GP = General Practitioner; and LVEF = Left Ventricular Ejection Fraction.

### 2.1 Patient and public involvement

A Steering Group was established to oversee the design, conduct, and reporting of the trial. This group comprises academics, carers, patients with HF, healthcare professionals, and representatives from patient and carer support organisations. During project delivery, HELP champions (carers who received the intervention) will be recruited across the collaborating sites to the Steering Group to provide input on their experience and any required intervention adaptations. A range of protected characteristics (*i.e.,* age, socio-economic status, and ethnicity) are and will be present across the members to ensure equality and diversity. The Steering Group will meet monthly and virtually over the project lifetime to provide critical assessment, monitoring, and consensus agreement on project delivery (*i.e.,* context-specific tailoring), issue resolution (*i.e.,* recruitment and retention), and dissemination activities. Communication between meetings will occur as required.

### 2.2 Design

A mixed-method, implementation study adopting a multi-centre prospective cohort study design, with nested process and economic evaluations will be conducted. The implementation strategy assessments will be underpinned by the integration of the Consolidated Framework for Implementation Research (CFIR) [13] and Normalisation Process Theory (NPT) [14], which will provide holistic insights into the macro (*i.e.,* system-level) and micro (*i.e.,* individual-level) factors influencing implementation outcomes [15].

#### 2.2.1 Setting.

This study will be conducted across five hospital sites spanning three regions of the UK (Northern Ireland, England, and Scotland). Local HF nurses will deliver HELP to carers of patients with HF within their corresponding region. The collaborating sites will constitute early adopters of HELP and will be designated as ‘Beacon Sites’. These Beacon Sites will be used to model programme implementation, which is a method of informing and supporting embedding of innovative practice [16]. The collaborating sites were selected due to their ability to commit to HELP implementation, to diversify sample inclusion, and increase geographic spread.

#### 2.2.2 Sample and recruitment.

This study will recruit participants across three populations: 1. Carers, 2. Patients with HF, and 3. Healthcare Professionals. In compliance with the Screened, Eligible, Approached, Randomised/ Recruited (SEAR) framework [17], anonymised screening and recruitment logs will be used to document numbers and percentages of eligible and recruited participants, along with reasons for non-participation and withdrawal. These data will be monitored by the Steering Group to identify recruitment barriers and inform necessary strategies to optimise enrolment across the collaborating sites.

#### 2.2.4 Carers.

The target population of HELP is informal carers of patients with symptomatic HF. These individuals will be eligible to participate if they are: 1) Aged 18 years or older; 2) Physically and mentally capable of operating a digital device; 3) Able to engage comfortably in conversation with peers and capable of reading written materials; 4) Caring (regular, unpaid care) for a person with a clinical diagnosis of HF who is receiving standard evidence-based HF therapies and has either HF symptoms or one episode of decompensation (symptoms requiring medical attention) in previous six months; and 5) Capable of speaking and understanding English.

There will be five programme rollouts of HELP (six weeks each) across each of the three collaborating nations over a one-year period, with twelve carers per rollout (60 carers per nation; 180 carers in total). This sample size was pragmatically determined by the maximum study duration within the funding limit, along with the recruitment rate demonstrated in the pilot study [10].

#### 2.2.5 Patients.

Patients who are receiving informal support from the recruited carers will be invited to participate via the provision of data, which will allow their perspectives on HELP implementation to be captured, whilst also facilitating an assessment of the potential, dyadic impact of the intervention. These patients will be eligible to participate if they are: 1) Aged 18 years or older; 2) Physically and mentally able to engage comfortably in conversation and capable of reading written materials; 3) Clinically diagnosed with HF and receiving standard evidence-based HF therapies and either have HF symptoms or one episode of decompensation (symptoms requiring medical attention) in previous six months; 4) Able to speak and understand English; and 5) Receiving regular, unpaid support with managing their condition from a loved one (*i.e.,* a relative or spouse) or friend. Patients will be ineligible if their carers refused to participate in HELP. Carers will remain eligible for participation regardless of patient enrolment. One patient per carer will be invited to participate to enhance sample diversity (approximately 180 patients in total).

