#### 2.2.6 Carer and patient recruitment.

Local cardiology teams will identify and approach potential participants during routine, in and out-patient HF appointments. Eligible patients will receive information packs for both them and their carer. Those interested in participation will provide permission to be contacted by the research team for recruitment. During this contact, patients will also signpost the research team to their interested carers. Subsequently, these carers will be contacted by the research team for eligibility screening and recruitment. The collaborating hospital sites cover regions with a range of socio-demographic characteristics (*i.e.,* education level, socio-economic status, and ethnicity), which will maximise the diversity of the recruited sample.

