#### 2.3.4 Participant outcomes.

The short and long-term impact of HELP on outcomes for carers and patients will be assessed across data from validated questionnaires, patient diaries, and medical records (see Table 2). Participant outcome data will be collected at three time points: 1. Baseline, 2. Post-intervention (week six), and 3. Six months post-intervention.

**Table 2 pone.0347037.t002:** Participant Outcomes and Measurement Instruments.

Sample	Outcome	Measurement Instrument	Time Point		
			Baseline	Post-Intervention (Week 6)	6 Months Post-Intervention
**Carers**	Carer Burden	Zarit Burden Interview, Short Form [26]	X	X	X
	Carer Preparedness	Preparedness for Caregiving Scale [27]	X	X	X
	QoL	12-Item Short Form Survey [28]	X	X	X
	Anxiety and Depression	Hospital Anxiety and Depression Scale [29]	X	X	X
	Stress	Perceived Stress Scale [30]	X	X	X
	Social Support	Multidimensional Scale of Perceived Social Support [31]	X	X	X
**Patients with HF**	Disease-specific, QoL	Minnesota Living with HF Questionnaire [32]	X	X	X
	Generic, QoL	EuroQoL Five Dimension Questionnaire [33]	X	X	X
	GP Visits with Reasons over Previous 6 Months	Bespoke, Recall Questionnaire at Baseline and Patient Diary Self-Completed from Baseline to 6 Months	X		X
	Most Recent LVEF Measurement	Medical Record	X		X
	Hospital Admissions with Reasons over Previous 6 Months	Medical Record	X		X

**Legend** QoL = Quality of Life; HF = Heart Failure; GP = General Practitioner; and LVEF = Left Ventricular Ejection Fraction.

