### 2.5 Data analysis

#### 2.5.1 Quantitative data.

Quantitative data analysis will be managed on Statistical Package for the Social Sciences (IBM SPSS Statistics, Version 31). Continuous data will be presented as mean ± standard deviation, with discrete data reported as absolute numbers and percentages. Categorical data will be displayed as frequency/ percentages. For participant outcomes, repeated measures analysis of variance will be used to investigate the effect of time point on outcome scores. Due to the absence of statistical power, the results will be used to identify preliminary evidence of promise for the intervention across different participant outcomes, with potential effect sizes generated to inform the required sample size for a future definitive evaluation.

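### Some patients are enrolled through an event inside the six-month window that forms the baseline for hospital admissions, so part of any fall in admissions after HELP would be regression to the mean

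*Protocol article*

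**What the plan says.** All references are to the protocol article.

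- **Entry.** Section 2.2.5 accepts patients who "either have HF symptoms or one episode of decompensation (symptoms requiring medical attention) in previous six months". Section 2.2.4 applies the same rule to the person the carer looks after, who "has either HF symptoms or one episode of decompensation (symptoms requiring medical attention) in previous six months".
- **Where patients are found.** Under section 2.2.6, local cardiology teams "identify and approach potential participants during routine, in and out-patient HF appointments".
- **Outcomes.** Table 2 in section 2.3.4 lists "Hospital Admissions with Reasons over Previous 6 Months", taken from the medical record, and "GP Visits with Reasons over Previous 6 Months". Both are recorded at baseline and at six months post-intervention.
- **Design.** Section 2.2 describes a "multi-centre prospective cohort study design, with nested process and economic evaluations". Every recruited carer receives HELP, so there is no comparison group.
- **Analysis and use.** Section 2.5.1 says that "repeated measures analysis of variance will be used to investigate the effect of time point on outcome scores" for participant outcomes. The results are to identify preliminary promise and to supply effect sizes for the sample size of a later definitive study.
- **Caveat.** Section 3.1 says the participant outcomes will not be definitive, citing the lack of randomisation and of statistical power.

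**The concern.** The eligibility look-back and the baseline look-back are both six months and largely coincide. A patient enrolled on the strength of a recent decompensation, or approached while in hospital, is partly selected on a high baseline value of the outcome. Nothing selects the follow-up six months in the same way. Such patients will on average have fewer admissions afterwards even if HELP does nothing, and with no control group the time effect cannot be separated from this selection.

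Two uses are at stake. A fall in admissions would match the benefit that section 3.0 hopes for and could be read as promise. If the same fall were carried forward as an effect size, the future study could be planned too small. Low power is a matter of imprecision, whereas this is bias in a known direction that a larger sample would not remove.

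**Working it through.** **What the plan supplies.** The only related figure is the sample size: 5 rollouts x 12 carers x 3 nations = 180 carers, which reproduces, with about 180 patients. The plan gives no admission rate, GP-visit rate or share of patients by entry route, so these are assumptions shown as ranges.

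**Model, with no HELP effect.** Each patient has a personal rate drawn from a gamma distribution with mean m per six months and shape k. Counts before and after are Poisson with that same rate. A share q is enrolled because of at least one admission in the baseline window; the remaining 1 - q is unselected.

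- Probability of no admission: p0 = (k/(k+m))^k
- Selected patients, baseline mean: B = m/(1 - p0)
- Mean rate among patients with no admission: e0 = mk/(k+m)
- Selected patients, follow-up mean: F = (m - p0 x e0)/(1 - p0)
- Whole sample: baseline = (1-q)m + qB; follow-up = (1-q)m + qF

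**Admissions, assumed m = 0.3 to 0.5 and k = 0.5 to 2.** The extremes lie at two corners.

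- Smallest fall, m = 0.5 and k = 0.5: p0 = 0.7071, B = 0.5/0.2929 = 1.707, e0 = 0.250, F = (0.5 - 0.7071 x 0.250)/0.2929 = 1.104.
- Largest fall, m = 0.3 and k = 2: p0 = 0.7561, B = 0.3/0.2439 = 1.230, e0 = 0.261, F = (0.3 - 0.7561 x 0.261)/0.2439 = 0.421.

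| q | m = 0.5, k = 0.5: before to after | Fall | m = 0.3, k = 2: before to after | Fall |
|---|---|---|---|---|
| 0 | 0.500 to 0.500 | 0% | 0.300 to 0.300 | 0% |
| 5% | 0.560 to 0.530 | 5% | 0.347 to 0.306 | 12% |
| 10% | 0.621 to 0.560 | 10% | 0.393 to 0.312 | 21% |
| 25% | 0.802 to 0.651 | 19% | 0.533 to 0.330 | 38% |
| 50% | 1.104 to 0.802 | 27% | 0.765 to 0.361 | 53% |

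**Sensitivity to the rate.** If the mean were as high as 1.0 with k = 1, then B = 2.0 and F = 1.5. The fall is 10% at q = 25% (1.25 to 1.125) and 17% at q = 50% (1.50 to 1.25).

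**Would it show in a test?** Admissions are recorded at two time points, so a repeated measures analysis reduces to a paired comparison. In a simulation with m = 0.5, k = 1, 180 complete pairs and no HELP effect, a two-sided 5% paired test declared a fall in 53% of runs at q = 25% and 97% at q = 50%.

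**GP visits.** With an assumed mean of 2 to 4 visits per six months and the same shapes, conditioning on at least one visit gives a fall of about 1-4% at q = 25% and 2-7% at q = 50%. Most patients would have a visit anyway, so the condition selects little.

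**An event-free subgroup.** Restricting to patients with no admission in the baseline window sets their baseline to 0 by construction. Their follow-up mean is e0, which runs from 0.3 x 0.5/0.8 = 0.19 to 0.5 x 2/2.5 = 0.40. Admissions would then appear to rise with no HELP effect.

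**The case against.** The strongest reply is that the size is unknown and could be small. Entry is either/or, the target population is carers of patients with symptomatic heart failure, and a symptomatic patient needs no event to qualify. A reader might infer that the whole sample is selected on a baseline event; the text does not support that. If nobody is enrolled because of an event, this mechanism adds nothing. This stands, and is why the table starts at q = 0. It does not dispose of the point, because symptomatic patients approached as in-patients also carry a recent admission.

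Second, a decompensation is defined by a need for medical attention, which could be a clinic contact counted in neither outcome. The model conditions on an admission, so it fits the in-patient approach and overstates the decompensation route. The two look-back windows also need not match day for day. Both points stand.

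Third, a reader might treat GP visits as equally affected. At plausible visit frequencies they are not. The change from recall at baseline to a diary afterwards ("Bespoke, Recall Questionnaire at Baseline and Patient Diary Self-Completed from Baseline to 6 Months") is a separate measurement question.

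Fourth, the plan is modest about these outcomes. The impact objective is exploratory, section 3.0 says only that HELP may reduce readmissions, and section 3.1 disclaims definitive findings. Section 2.5.1 speaks of outcome scores, so a formal test on admission counts is an inference, and nothing singles out admissions as the basis for the next sample size. This lowers the stakes. However, Table 2 lists admissions among the participant outcomes, section 2.5.1 puts those outcomes to both uses without exception, and the caveat names neither selection on the baseline count nor the direction of the bias.

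**Conclusion.** The point holds for hospital admissions, as a directional bias of unknown size. With no HELP effect and the assumed rates (mean 0.3 to 0.5 per six months, gamma shape 0.5 to 2), the built-in fall is 0% at q = 0, 5-12% at q = 5%, 10-21% at q = 10%, 19-38% at q = 25% and 27-53% at q = 50%. These are upper figures for patients who enter by decompensation, and a higher true rate makes them smaller. For GP visits the effect is probably slight.

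It would go too far to say that any observed fall must be artefact, or that the plan presents fewer readmissions as an expected result. The documents support only this: part of a fall would be regression to the mean, the uncontrolled design cannot say how much, and the stated caveat does not alert the reader to it. Acting on it is a cheap improvement, not a condition for the study to proceed.

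**What to change.** 1. State that the before-after contrast in hospital admissions will not be used as evidence of promise or as an effect size for the future study.
2. Report the follow-up admission rate per unit of person-time with a 95% confidence interval, as a planning input.
3. Record for each patient the entry route (symptoms, decompensation, in-patient approach) and the date of any index admission or qualifying episode, so that q is known.
4. If a before-after figure is shown, show it for all patients, with the event-selected share beside it and an explicit regression-to-the-mean caveat. Do not show it for an event-free subgroup, which builds in the opposite bias.
5. Add selection on the baseline count to the limitations in section 3.1.

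The cost is one case report form field and some analysis wording, with whatever approval section 2.6 requires for an amendment. The field is best in place before recruitment, expected from 01/04/2026, because the entry route may be hard to reconstruct later. The downside is the loss of a favourable-looking but biased contrast. Eligibility and care are unchanged.
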